### Sample size considerations

Based on the most recent meta-analysis, we expect a pain response in 60% of patients following standard radiotherapy [3]. Pain response after stereotactic radiotherapy is assumed to be 85% [8, 9]. We expect that approximately 90% of patients who are offered SBRT treatment, will accept the offer. Cross-over from control arm to the SBRT treatment arm is extremely unlikely, since only patients who are randomly selected to receive SBRT are informed about the treatment. Taking a one-sided α of 5% and a power of 80%, we require 49 patients per treatment arm to show a statistically significant difference of 15% in pain response. The reason to choose a one sided α is that, although improbable, inferior pain response after stereotactic treatment would lead to the same action as no difference at all between the two treatment regimen. This is because the SBRT treatment will only be implemented if it is significantly better than the usual care, since SBRT treatment is more complex, less convenient for patients, and more expensive than standard radiotherapy. Finally, to allow for a 10% drop out rate, recruitment of 55 patients per group is intended. We expect to complete recruitment within 18 months based on the number of patients we treat in our center annually.

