### Data analysis

Data will be analyzed according to the intention to treat principle. Data of eligible patients who were randomly offered stereotactic radiotherapy will be compared with eligible patients who were not randomly selected and received standard radiotherapy. In case of dropout (i.e. patients not surviving longer than three months or patients unable to provide pain scores and analgesic use), a worst-case analysis will be performed: dropped-out patients will be classified as non-responders. In case of substantial refusal of the SBRT offer in the intervention arm, instrumental variable analysis will be used to account for non-compliance [26]. The primary outcome (i.e. proportion of patients with response to radiotherapy) will be presented in absolute numbers and proportions. Differences in pain response will be compared by χ2 test. If randomization fails, imbalances between baseline characteristics will be adjusted by logistic regression analysis. Differences in duration of response and overall survival will be analysed by Kaplan-Meier analysis and log rank test. Toxicity will be presented as the overall incidence of grade 3–4 toxicity and incidence of vertebral compression fractures. Differences will be tested with the χ2 test. A comparison in QOL will be made between the baseline QOL and at predefined intervals after treatment. A change of 10% of the scale breadth will be considered a clinically relevant change of QOL [27]. Data will be presented as improved (≥10% increase), stable, or worsened (≥10% decrease) QOL. We will evaluate the pattern of QOL as a continuous outcome over time using mixed models. Differences with a *P*-value <0.05 will be considered statistically significant. We have planned to perform an interim analysis after inclusion of half of the patients (i.e. 55 patients) when they have completed their follow up (i.e. three months pain assessment).

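### The one-sided 5% rule that sizes the trial is not carried into the primary analysis, whose χ² test at P<0.05 is in its usual form two-sided and would have about 70% power, not 80%, at 49 per arm

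*Protocol article*

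**What the plan says.** Sample size considerations in the protocol article fixes the error rate and the size: "Taking a one-sided α of 5% and a power of 80%, we require 49 patients per treatment arm". It then defends the one-sided choice on the ground that "inferior pain response after stereotactic treatment would lead to the same action as no difference at all between the two treatment regimen", adding that SBRT would be adopted only if it proved significantly better than usual care.

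The rates given there are "we expect a pain response in 60% of patients following standard radiotherapy" for the control arm, an assumed 85% response after SBRT, and acceptance of the SBRT offer by about 90% of those selected. A 10% allowance for dropout raises 49 to 55 per arm.

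Data analysis gives the primary test as "Differences in pain response will be compared by χ2 test". It also names the χ² test for toxicity. After the sentences on survival, toxicity and quality of life, it closes with one threshold for everything: a P-"value <0.05 will be considered statistically significant". It gives no sidedness for any test. It also classes dropouts as non-responders, and it plans an interim analysis at 55 patients.

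**The concern.** The χ² statistic for a 2×2 table squares the difference, so its ordinary P value ignores direction. Declaring significance at P<0.05 then gives 2.5% in favour of SBRT, half of what the sample size section allows. An analyst who follows Data analysis literally, using the default output of any package, does not run the test for which the trial was powered.

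Two things are at stake. First, the stated 80% power may not be the power of the analysis performed. Second, there is a band of results in which the primary conclusion depends on which section is followed. If the rule is not fixed beforehand, a result in that band cannot be interpreted cleanly. The interim analysis brings the question forward to half of recruitment.

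**Working it through.** **Inputs.** From Sample size considerations: control response 60%; SBRT response 85%; acceptance 90%; one-sided α 5%; power 80%; 10% dropout. Allocation is 1:1 (Random selection).

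**Derived input (an assumption, not stated in the article).** Those who decline receive standard radiotherapy, so the intention-to-treat response in the offered arm is 0.9 × 85% + 0.1 × 60% = 82.5%.

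**Formula.** Normal approximation with pooled variance under the null and no continuity correction:

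n = [z(α)·√(2p̄(1−p̄)) + z(power)·√(p₁(1−p₁) + p₂(1−p₂))]² / (p₂−p₁)²

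With p₁ = 0.60 and p₂ = 0.825, p̄ = 0.7125, 2p̄(1−p̄) = 0.4097 and p₁(1−p₁) + p₂(1−p₂) = 0.3844.

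**Step 1: reproduce the plan's figure.** One-sided 5% (z = 1.645), power 80% (z = 0.842):

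(1.645 × 0.6401 + 0.842 × 0.6200)² / 0.225² = 48.98, so 49 per arm. Then 49/0.9 = 54.4, so 55. Both match.

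**Step 2: power of a two-sided 5% χ² test at 49 per arm.** The null standard error is √(0.4097/49) = 0.0914; under the alternative it is √(0.3844/49) = 0.0886.

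- One-sided: Φ[(0.225 − 1.645 × 0.0914)/0.0886] = 80.0%
- Two-sided: Φ[(0.225 − 1.960 × 0.0914)/0.0886] = 69.7%

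Exact binomial enumeration of the uncorrected χ² test gives 80.6% and 70.3%.

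The observed difference needed (at p̄ = 0.7125) is 1.645 × 0.0914 = 15.0 points one-sided and 1.960 × 0.0914 = 17.9 points two-sided. Keeping 80% power two-sided needs n = 62.3, so 63 per arm, or 63/0.9 = 70 with dropout.

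**Step 3: vary the conditions.** Dropouts count as non-responders, so all 55 per arm may enter the test. If 10% drop out in each arm, the rates become 0.9 × 60% = 54% and 0.9 × 82.5% = 74.25%.

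| Scenario | One-sided 5% | Two-sided 5% |
|---|---|---|
| 49 per arm, 60% vs 82.5% | 80.0% | 69.7% |
| 55 per arm, 60% vs 82.5% | 84.0% | 74.8% |
| 55 per arm, 54% vs 74.25% | 72.0% | 60.3% |
| 49 per arm, 60% vs 85% (acceptance ignored) | 88.0% | 80.1% |

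In the first three rows the gap is 9 to 12 points. The last row shows that 49 per arm also arises from a two-sided test of 60% versus 85%.

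**Step 4: can the verdict change?** Take 33 of 55 control and 42 of 55 SBRT responders. The difference is 9/55 = 0.1636, the pooled rate 75/110 = 0.6818, the standard error 0.0888, and z = 1.84. One-sided P = 0.033; χ² P = 0.065. The result is positive by the first rule and not significant by the second. At the design rates, the chance of landing in this band is the difference between the two exact powers: 80.6% − 70.3%, about 10%, at 49 per arm; 84.8% − 75.4%, about 9%, at 55.

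**The case against.** A reader might infer that the article prescribes a two-sided primary test, that the two sections flatly contradict each other, and that power is therefore 70%. The text does not support that. The term two-sided appears nowhere. Both sections use 5%, and a one-sided P value taken from the signed square root of χ² and judged at 0.05 would satisfy both. The P<0.05 sentence reads as a general closing convention, whereas the sample size section argues a specific rule for pain response, and a specific rule normally governs a generic one. This part of the objection stands.

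It can also be said that a condensed article leaves such detail to the full protocol or analysis plan. That holds only in part. The article itself states the α, the test and the threshold, and the usual form of that test at that threshold does not deliver the stated power. The same test and threshold also serve toxicity, where the argument for a one-sided test does not apply, so the reader cannot assume that the closing sentence is one-sided throughout.

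The power figure is not unique either. The 82.5% is derived, and 60% versus 85% tested two-sided gives 49 per arm with nothing lost. But that route conflicts with "Taking a one-sided α of 5% and a power of 80"% and ignores the stated acceptance rate. It shows only that the number 49 cannot by itself settle which test was meant.

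Finally, falling back on a two-sided test is the conservative direction. It cannot produce a positive result for SBRT that the one-sided rule would deny, so the false-positive risk in favour of SBRT stays within 5% under either rule. This is right. The issue is lost power and an unsettled decision rule, not an inflated error rate.

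**Conclusion.** The concern holds as a one-sided rule that is stated and justified for the design but not carried into the primary analysis. It does not hold as an explicit contradiction.

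If the χ² test is read in its usual two-sided form, and the intention-to-treat rates are 60% and 82.5%, power at 49 per arm is about 70% instead of 80%. With 55 per arm analysed, it is 75% instead of 84% at those rates, or 60% instead of 72% if 10% per arm drop out and count as failures. If the analysis is in fact run one-sided at 5%, nothing is lost. On either reading of the intent, a χ² P value between 0.05 and 0.10 in favour of SBRT currently has no settled interpretation. At the design rates, about one trial in ten would end there.

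**What to change.** Settle the rule before any data are analysed, including the interim, in one of two ways.

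- **If the one-sided design is intended:** add to Data analysis that the primary endpoint is tested one-sided at 5% in favour of SBRT (equivalently, χ² P<0.10 with the higher response proportion in the SBRT arm) and reported with a 90% confidence interval for the difference in proportions. State that P<0.05, two-sided, applies to the secondary endpoints.
- **If a two-sided primary test is intended:** amend the one-sided statement in Sample size considerations and restate the power at 49 per arm as about 70%. Keeping 80% would instead take 63 per arm, or 70 after the dropout allowance.

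The first option costs one sentence and no patients. The second costs a less favourable stated power, or 15 more patients per arm (70 − 55) if 80% is to be kept. In either case, the 82.5% should be written down as the assumed intention-to-treat rate, so that the calculation can be checked.

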**Methods/design:**

This study follows the ‘cohort multiple Randomized Controlled Trial’ design. The VERTICAL study is conducted within the PRESENT cohort. In PRESENT, all patients with bone metastases referred for radiation therapy are enrolled. For each patient, clinical and patient-reported outcomes are captured at baseline and at regular intervals during follow-up. In addition, patients give informed consent to be offered experimental interventions. Within PRESENT, 110 patients are identified as a sub cohort of eligible patients (i.e. patients with unirradiated painful, mechanically stable spinal metastases who are able to undergo stereotactic radiation therapy). After a protocol amendment, also patients with non-spinal bony metastases are eligible. From the sub cohort, a random selection of patients is offered stereotactic radiation therapy (*n* = 55), which patients may accept or refuse. Only patients accepting stereotactic radiation therapy sign informed consent for the VERTICAL trial. Non-selected patients (*n* = 55) receive standard radiotherapy, and are not aware of them serving as controls. Primary endpoint is pain response after three months. Data will be analyzed by intention to treat, complemented by instrumental variable analysis in case of substantial refusal of the stereotactic radiation therapy in the intervention arm.

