## Methods/design

### Study design

This study is conducted within the Prospective Evaluation of interventional StudiEs on boNe meTastases (PRESENT) cohort [12]. All patients with bone metastases referred to the departments or radiation oncology or orthopedic surgery of the University Medical Center Utrecht are asked to participate in this prospective, observational cohort. Baseline and follow-up data are collected from clinical files, and patient-reported outcomes (PROMs, i.e. a pain inventory and QOL questionnaires) are collected at fixed time intervals. This study follows the cohort multiple randomized controlled trial (cmRCT) design as described by Relton and colleagues [13].

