### Patient recruitment

At enrollment, patients give informed consent for collection of clinical and survival data, and can opt-in to provide PROMs. In addition, in a separate question, we ask patients for their broad consent for future randomization in trials that will investigate the effectiveness of experimental treatments [14]. Patients within the PRESENT cohort who meet the VERTICAL inclusion criteria (Table 1) are identified as a sub cohort of eligible patients. Eligible patients are PROMs-providing participants of the PRESENT cohort, have untreated symptomatic spinal metastases, and have given consent for broad randomization to experimental interventions. Patients are excluded if they are not able to undergo SBRT, have severe or progressive neurological deficits, received previous radiotherapy or surgery to the index site(s), or have a life expectancy less than three months. After a protocol amendment on September 23, 2015 to adjust to developments in clinical practice, also patients with non-spinal bony metastases are eligible.

**Table 1 Tab1:** Selection criteria for the VERTICAL study

Inclusion criteria	Exclusion criteria
Participant in PRESENT cohort	Lesion in C1, and C2
Filling out PRESENT-questionnaires	Contraindication for MRI if MRI is indicated
Broad consent for randomization to experimental interventions	Radiosensitive histology such as multiple myeloma
Histologic proof of malignancy	Unable to undergo SBRT treatment
Imaging evidence of bone metastases	Patient with < 3 months life expectancy
For spinal lesions, per lesion no more than 3 consecutive spine segments involved with one unaffected vertebral body above and below	Chemotherapy or systemic radionuclide delivery within 24 h before and after SBRT
No more than 2 painful lesions needing treatment	Previous EBRT or SBRT to same level
For spinal lesions, no compression of spinal cord	For spinal lesions, unstable spine requiring surgical stabilization
No or mild neurological signs^a^	Severe, worsening or progressive neurological deficit
KPS > 50 and pain score > 3^b^	

*VERTICAL* randomized controlled trial comparing conVEntional RadioTherapy with stereotactIC body radiotherapy in patients with spinAL metastases; *PRESENT* Prospective Evaluation of interventional StudiEs on boNe meTastases (PRESENT) cohort; *MRI* magnetic resonance imaging; *SBRT* stereotactic body radiotherapy; *EBRT* external beam radiotherapy; *KPS* Karnofsky performance score

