### Random selection

Eligible patients are randomly selected from the sub cohort on a 1:1 basis with varying block sizes (*n* = six or eight) using an in-house randomization computer program. The radiation oncologist will offer the experimental intervention (i.e. SBRT) to the randomly selected patients. If they accept the treatment offer, they will sign informed consent for participation in the VERTICAL study. Patients who refuse the SBRT will receive care as usual (i.e. standard radiotherapy). According to the cmRCT design, patients in the sub cohort who are not randomly selected will not be informed about the experimental intervention, nor will they be informed about their participation in the control arm of the VERTICAL study. Outcomes in randomly selected patients are compared with the outcomes in eligible patients not randomly selected who received standard radiotherapy (Fig. 1).

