### Primary endpoint

Primary endpoint of this study is complete or partial pain response at three months. Pain response is defined according to the International Bone Metastases Consensus Endpoints for Clinical Trials (Table 2) [19]. A pain score of zero with no concomitant increase in analgesic intake compared to baseline is defined as complete response. Partial response is pain reduction of at least two points on a scale of 0–10 without increase in analgesic intake and/or analgesic reduction of at least 25% from baseline without an increase in pain. Pain progression is defined as an increase in pain score of at least two points above baseline with stable analgesic use and/or as an increase of at least 25% in analgesic use compared to baseline with at least stable pain scores. All responses not captured with complete and partial response or pain progression are considered indeterminate response. Pain is measured by the Brief Pain Inventory (BPI), which has been validated for use in advanced cancer patients to assess pain and functional interference stemming from bone metastases [20].

**Table 2 Tab2:** Response rate to radiotherapy according to the international consensus [19]

Responders	
Complete response	Pain score of 0 and stable or reduced OMED
Partial response	Pain reduction of 2 points on a 0–10 scale or more and/or OMED reduction by 25% or more
Non-responders	
Pain progression	Increase of 2 points on a 0–10 scale or more above baseline, and/or OMED increased by 25% or more
Indeterminate response	Any response including stable disease that is not captured by complete or partial response or pain progression

*OMED* daily oral morphine equivalent

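### Baseline adjustment of the primary comparison depends on an undefined failure of randomisation; a short covariate list should be fixed in advance

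*Protocol article*

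**What the plan says.** The endpoint is binary: "Primary endpoint of this study is complete or partial pain response at three months" (Primary endpoint). The default test is unadjusted: "Differences in pain response will be compared by χ2 test" (Data analysis). The next sentence of that section adds the conditional step: "If randomization fails, imbalances between baseline characteristics will be adjusted by logistic regression analysis". The article does not say what counts as failure, how imbalance is judged, or whether the adjusted estimate replaces the χ2 result or sits beside it.

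Allocation is described under Random selection: "Eligible patients are randomly selected from the sub cohort on a 1:1 basis with varying block sizes", with blocks of six or eight. No stratification factor is mentioned. Since the September 2015 amendment, "also patients with non-spinal bony metastases are eligible" (Patient recruitment).

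On baseline data, the Abstract says of each patient that "clinical and patient-reported outcomes are captured at baseline and at regular intervals during follow-up". Under Secondary endpoints, the Brief Pain Inventory (BPI) is completed before radiation starts. Completing the cohort questionnaires is an inclusion criterion (Table 1). Response is defined against baseline pain and baseline analgesic intake (Table 2), so both must be on file for anyone whose response is assessed.

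**The concern.** Under correct randomisation some baseline differences are expected, and the error rate of the unadjusted test already allows for them. Calling such differences a failure confuses chance with a fault in the procedure. If allocation really had broken down, regression on a few measured variables would not restore it.

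Observed imbalance is also a poor way to choose covariates. What makes adjustment worthwhile is how strongly a variable predicts response, and that can be judged before any data are seen. A rule driven by imbalance may adjust for something irrelevant and leave out the baseline pain score because it happened to be balanced.

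At stake are a primary-outcome analysis that is fully fixed in advance and whatever precision the collected baselines could add in a trial of 110. A logistic model would also ordinarily yield a conditional odds ratio, a different effect measure from the proportions the section says it will present.

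**Working it through.** **1. The plan's own figure.** Inputs from Sample size considerations: "we expect a pain response in 60% of patients following standard radiotherapy", 85% after SBRT, 90% acceptance of the offer, one-sided α 5%, power 80%, 10% dropout.

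- Intention-to-treat rate in the offered arm: 0.9 × 0.85 + 0.1 × 0.60 = 0.825.
- n per arm = [z₀.₉₅ √(2p̄(1−p̄)) + z₀.₈₀ √(p₀(1−p₀) + p₁(1−p₁))]² / (p₁−p₀)², with p̄ = 0.7125.
- = [1.645 × 0.640 + 0.842 × 0.620]² / 0.225² = 1.575² / 0.0506 ≈ 49.
- 49 / 0.9 = 54.4, rounded up to 55.

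So 49 and 55 reproduce with an unadjusted two-proportion test. The 15% difference printed in that section does not match these inputs; that is a separate matter and is not used here.

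**2. Power of the unadjusted test at 55 per arm.**

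- 60% vs 82.5%: z = (0.225 × √55 − 1.645 × 0.640) / 0.620 = 0.99, power 84.0%.
- Data analysis counts dropouts as non-responders. With 10% dropout the rates become 0.9 × 0.60 = 54% and 0.9 × 0.825 = 74.25%. Pooled SE 0.0915, alternative SE 0.0894: z = (0.2025 − 1.645 × 0.0915) / 0.0894 = 0.58, power 72%.

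**3. How often chance alone would trip the clause.** The article gives no criterion. Assume that failure means any baseline p < 0.05 among k independent characteristics. The chance is then 1 − 0.95^k: 5% for k = 1, 14% for 3, 23% for 5 and 40% for 10.

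**4. Power under three rules** (simulation, 55 per arm, one-sided 5%, normal covariates). Prognostic strength is assumed throughout. The conditional rule adjusts only for covariates with baseline p < 0.05.

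Three covariates, 60% vs 82.5%, 4,000 replicates:

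| Combined SD on logit scale | χ2 | Always adjusted | Conditional |
|---|---|---|---|
| 0.5 | 85.7% | 86.2% | 85.5% |
| 1.0 | 84.3% | 88.2% | 84.2% |
| 1.5 | 85.3% | 92.6% | 86.0% |

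One covariate, 54% vs 74.25%, 6,000 replicates:

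| Odds ratio per SD | χ2 | Always adjusted | Conditional |
|---|---|---|---|
| 1.65 | 71.8% | 73.4% | 71.9% |
| 2.2 | 71.5% | 76.1% | 72.0% |
| 2.7 | 71.8% | 78.4% | 72.4% |

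With a covariate of no prognostic value (odds ratio 1.0) a separate run gave no gain: 73.0% against 73.2%. Always adjusting therefore gains about 0 to 7 points (largest 92.6 − 85.3 = 7.3). The conditional rule gains at most 86.0 − 85.3 = 0.7.

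A further run with three covariates, using both the Wald test and a standardised risk difference, moved power from about 72% to 72–79% and from about 84–85% to 84–88%.

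**5. Type I error** (60% in both arms, three covariates): χ2 4.8–5.1%, always adjusted 4.7–5.4%, conditional 4.4–4.8%. The run with the standardised risk difference gave 4.6–5.5%. With five covariates the always-adjusted test rose to 5.9–6.4%, against 4.8–5.7% for χ2 in the same runs. That argues for a short list, as does the expected number of non-responders: 0.46 × 55 + 0.2575 × 55 ≈ 39.

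**The case against.** The strongest reply is that the primary test is already fixed. The χ2 sentence carries no condition, the sample size reproduces with that test, and an unadjusted comparison is valid under 1:1 randomisation with no stratification factor named. On this view the logistic step is a supportive analysis, and its details belong in an analysis plan that is not shown. Much of this stands: the covariate list and the exact imbalance criterion are not counted as omissions here. What the reply does not remove is the trigger itself, which the article states. An analysis plan that kept it could not also make adjustment independent of observed balance.

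Four stronger readings are tempting and are not supported:

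- **The headline result is left open until baseline data are seen.** The article never says that the adjusted result replaces the χ2 result; it only leaves their relation unstated.
- **The clause inflates false positives.** A mechanical trigger did not. Error rose to 5.6–7.6% (three covariates) only when the better of the adjusted and unadjusted results was reported, and nothing in the article permits that.
- **Power is certainly thrown away.** No prognostic strength is given for any baseline variable, and weak covariates bring almost nothing.
- **Mixing spinal and non-spinal disease makes site a necessary covariate.** The Discussion expects similar response in both, so site is the least supported candidate.

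**Conclusion.** The point holds as a defect in how adjustment is specified; it does not make the primary test invalid. The clause treats chance imbalance as failed randomisation, selects covariates after the data are seen, leaves the adjusted result's standing unclear, and recovers essentially none of the precision that adjustment could provide. The cost is loss of prespecification plus about 0 to 7 points of power at 55 per arm.

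The power range assumes normally distributed, independent covariates and the prognostic strengths shown. The simulations used one or three covariates for power, not the exact two-variable model recommended here. The gain matters more if the dropout rule bites as planned, since unadjusted power is then about 72%, below the 80% target; without dropout it is about 84%.

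**What to change.** Delete the failure condition. Prespecify, whatever the observed balance, a primary logistic model on randomised arm with baseline BPI pain score and baseline analgesic use (daily oral morphine equivalent). Report it as a standardised (marginal) risk difference with its confidence interval, so that the result stays on the scale of proportions. Keep the unadjusted χ2 test as a sensitivity analysis and say so. Index site (spinal or non-spinal) may be added as a third covariate but is optional; the list should not grow beyond that.

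The change should be fixed before outcomes are compared by arm. No new data are needed. The cost is a revised paragraph and slightly more analysis work. The downside is that nothing is gained in power if the two baselines turn out to be only weakly prognostic.

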### Secondary endpoints

Secondary endpoints include local tumor control, duration of pain response, toxicity, vertebral compression fractures, QOL, and overall survival. Evaluation of local tumor control will be based on imaging acquired during follow-up. Duration of pain response starts at response until pain progression or end of follow-up using information provided by the BPI. A radiation oncologist records toxicity according to the National Cancer Institute’s Common Terminology Criteria for Adverse Events, version 4.0 [21] six weeks after radiation treatment. Toxicity occurring after 6 weeks, (serious) adverse events (SAEs), and hospitalization are registered in the context of the PRESENT cohort. Information about toxicity is based on clinical follow-up data and biannual patient-administered questionnaires on health status and hospitalization. All patients in the SBRT arm undergo an additional MRI scan six months after radiation in order to assess vertebral compression fractures. Since most compression fractures occur four months after radiation treatment [22], this 6-month-MRI captures most incidents. In case of clinical suspicion of a vertebral compression fracture, obtaining the MRI scan will be advanced as deemed appropriate. Quality of life is measured by the EORTC QLQ-C15-PAL general questionnaire [23] and the bone metastases-specific module, the EORTC QLQ-BM22 [24]. The EORTC QLQ-C15-PAL is an abbreviated 15-item version of the EORTC QLQ-C30 specially developed for use in palliative care. In order to evaluate the cost-effectiveness, patients are also provided with the EQ-5D questionnaire. Patients fill out these QOL questionnaires and the BPI before the start of radiation treatment (baseline) and after one, two, three, and six months, and every six months thereafter. The BPI is provided after two and six weeks as well. We make use of the digital patient tracking system PROFILES, so patients are able to complete the questionnaires online after secured login [25]. Overall survival is monitored within the PRESENT cohort by clinical follow-up and via an electronic link with the Municipal Personal Records Database.

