### Safety

We will report treatment induced SAEs within 15 days following notification through a government based internet portal to the accredited institutional review board that approved the protocol. Treatment induced SAEs that result in death or are life threatening will be reported within seven days.

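### The toxicity comparison stops at grade 4, so a treatment-induced event recorded only as fatal is not counted in it (minor)

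*Protocol article*

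**What the plan says.** The protocol article deals with harm in three places.

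- **Secondary endpoints** names the grading scale: "A radiation oncologist records toxicity according to the National Cancer Institute’s Common Terminology Criteria for Adverse Events, version 4.0", recorded six weeks after treatment. For anything later: "Toxicity occurring after 6 weeks, (serious) adverse events (SAEs), and hospitalization are registered in the context of the PRESENT cohort".
- **Safety** covers expedited reporting to the review board and foresees fatal events: "Treatment induced SAEs that result in death or are life threatening will be reported within seven days".
- **Data analysis** fixes what is compared: "Toxicity will be presented as the overall incidence of grade 3–4 toxicity and incidence of vertebral compression fractures". It continues: "Differences will be tested with the χ2 test".

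Deaths enter the planned analyses in two other ways, both also in Data analysis. One is survival: "Differences in duration of response and overall survival will be analysed by Kaplan-Meier analysis and log rank test". The other is the primary endpoint, where patients who do not survive longer than three months are treated as dropouts: "dropped-out patients will be classified as non-responders".

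**The concern.** The analysis rule sets both ends of the range of grades. It is therefore a stated rule, not a detail left open for a later document. The article expects that treatment-induced events may be fatal and arranges to report them, but the sentence defining the between-arm toxicity comparison has no place for them.

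At stake is the completeness of the harm result. The Discussion describes the biological effective dose of the SBRT schedules as much above that of conventional treatment, and the section on SBRT gives spinal cord constraints first priority. Readers will look to the toxicity comparison for the most serious harms, and the rule as worded leaves out the gravest category.

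**Working it through.** **Is the event recovered elsewhere?** The places where a treatment-induced death could appear:

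| Place in the article | What it does with the death | Between-arm toxicity comparison? |
|---|---|---|
| Safety | Report to the review board within seven days | No, reporting only |
| Secondary endpoints | Registration in the PRESENT cohort | No, data capture; no test stated |
| Data analysis, survival | Kaplan-Meier and log rank, all causes | No, not attributed to treatment |
| Data analysis, dropout rule | Non-responder if within three months | No, an efficacy outcome |
| Data analysis, compression fractures | Counts fractures | Does not capture a fatal toxicity as such |
| Data analysis, graded toxicity | Counts grades 3 and 4 | Yes, but the fatal category is outside the range |

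**Assumption on grading.** The article names the scale but does not print its grade definitions. The reading here is that a fatal event is recorded in a category beyond grade 4. If the investigators recorded fatal events as grade 4, nothing would be lost.

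**Inputs.** The article gives no toxicity rate to reproduce. The only figure needed is the arm size. Sample size considerations gives 49 per arm before dropout ("Taking a one-sided α of 5% and a power of 80%, we require 49 patients per treatment arm"), and with 10% dropout 49/0.90 = 54.4, rounded up to 55, as planned.

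**Size per event.** One uncounted patient is 1/55 = 1.8 percentage points in that arm (1/49 = 2.0 points if only 49 contribute).

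**Illustrations.** All counts are assumptions, SBRT v control, 55 per arm. P values are from the χ2 test without continuity correction.

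| Grade 3–4 | Fatal only | As written | Fatal included |
|---|---|---|---|
| 3 v 3 | 1 v 0 | 5.5% v 5.5%, P = 1.00 | 7.3% v 5.5%, P = 0.70 |
| 3 v 3 | 0 v 1 | 5.5% v 5.5%, P = 1.00 | 5.5% v 7.3%, P = 0.70 |
| 3 v 0 | 1 v 0 | 5.5% v 0%, P = 0.079 | 7.3% v 0%, P = 0.042 |
| 5 v 2 | 3 v 0 | 9.1% v 3.6%, P = 0.24 | 14.5% v 3.6%, P = 0.047 |

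For x events against none with 55 per arm, the uncorrected statistic reduces to χ2 = 110x/(110 − x).

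- x = 3: 330/107 = 3.08, P = 0.079.
- x = 4: 440/106 = 4.15, P = 0.042.

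**How firm is the crossing of 0.05?** For 4 v 0 the expected number of events is 4 × 55/110 = 2 per arm, which is small for a χ2 approximation.

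- Continuity-corrected: 110(x − 1)²/[x(110 − x)] = 990/424 = 2.33, P about 0.13.
- Fisher, two-sided: 2 × C(55,4)/C(110,4) = 2 × 0.059 = 0.12.

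Neither crosses 0.05. The article does not say whether its χ2 test is corrected.

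**The case against.** The other side has several fair points.

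- **A reader might infer that a patient who goes from grade 4 to death drops out of the count.** The article does not support this. It states no worst-grade rule and nothing by which a later grade cancels an earlier one, so a patient with a grade 3 or 4 event on record before death can still be counted. Only an event recorded solely as fatal is left out.
- **A reader might infer that the rule favours SBRT.** This is not supported either. Within an arm, the omission can only lower the rate. Between arms, it helps whichever arm has more uncounted fatal events, as the second row of the table shows. The article gives no fatal toxicity rate for either arm.
- **A reader might infer that one death could readily change the test result.** That happens only in a table chosen for the purpose, and only with the uncorrected χ2 test. In the balanced one-death example the rates barely move.
- **Fatal events are not lost from the trial.** This is correct. They are reported, registered and counted in survival. What remains is that none of these is a comparison of toxicity between arms.
- **The article is condensed.** Per-patient counting rules and listings of deaths are commonly left to the full protocol or analysis plan, and their absence here is no fault. The upper bound on the grades is different, because the article states it.

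**Conclusion.** The point holds in a narrow form. As worded, the between-arm toxicity comparison excludes a treatment-induced event recorded only as fatal, although the article foresees such events, and no other planned analysis brings it back as a toxicity. Each such event understates its arm's severe-toxicity rate by 1.8 points with 55 per arm, and the effect on the difference between arms may go in either direction.

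The conclusion assumes that fatal events are recorded beyond grade 4 and that the stated range is applied literally. How often this would matter cannot be judged from the article. Toxicity is a secondary endpoint, the sample size was set for pain response, and fatal toxicity may be rare. The severity is minor.

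**What to change.** In Data analysis, replace grade 3–4 with grade 3 or higher, state that fatal treatment-related events are included, and count each patient once. The full protocol or analysis plan can carry any further detail, such as a listing of treatment-related deaths by arm.

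The cost is a short change of wording. CTCAE grading and registration of serious adverse events are already planned, so no new data are needed, and treatment and sample size are unaffected. The change is best made before toxicity is compared between arms, so that including fatal events does not look like a choice made after seeing them.
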